### Trial committees

[name] guides the research team and provides overall supervision for the trial. The data monitoring committee ([name], [name], [name], and [name]) is responsible for reviewing and monitoring data safety. They need to make sure that all CRFs are filled out correctly and consistent with the original data and that all adverse events have been recorded and all serious adverse events have been reported in accordance with the relevant procedures. Investigators have the right to reveal a participant’s allocated intervention or terminate the study in advance after discussion with [name] in the event of safety issues during the study as well as notify the ethics committee.

### Amendments

The protocol should be strictly implemented as it has been approved by the ethics committee. If it is necessary to add or revise the study protocol after the start of the study, the investigator should submit it to the ethics committee again and obtain approval before implementation. The modification of the protocol will be recorded in detail. The trial was registered on 9 October 2018 and updated on 2 March 2020 (URL: http://www.chictr.org.cn).

### Auditing and dissemination policy

To ensure the trial is carried out in accordance with the standard operating procedures and corresponding regulatory requirements, an independent audit, i.e., systematic and independent review of research-related activities and documents, can take place at the research center at any time during or after the end of the study. The trial results will be published in the form of a paper or presentation, and the name of the patients and other personal information will not be disclosed (excluding the date of birth/age and gender).

## Statistical considerations

### Sample size

We use the URL (https://www.cnstat.org/samplesize/5/) to generate the calculated sample size. According to our pre-experimental results, we assume *α* = 0.05, 1-*β* = 0.80, Mean_*t*_ = 20, Mean_*c*_ = 40, *σ* = *S*_*t*_ = *S*_*c*_ = 20, *N*_t_:*N*_c_ = 1:1, and suppose that a 20% IMR reduction (Δ = − 8) is considered of clinically meaningful difference. We get approximately 36 (between 35 and 36) needed patients in each group. Considering the loss rate of 10%, the total sample size will be 78 cases with 39 cases in each group. The equation being used to estimate the sample size is as follows:
$$ n=\frac{2{\left({Z}_{\alpha }+{Z}_{\beta}\right)}^2{\sigma}^2}{{\left({\mathrm{Mean}}_t-{\mathrm{Mean}}_c-\Delta \right)}^2}. $$

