### Analysis

All data will be presented as percentages, mean ± standard deviation (SD), or median (quartile range). As the population variance *σ*^2^ is unknown, the confidence interval of the population mean *μ* is calculated by the formula $$ \overline{X}\pm \frac{S}{\sqrt{n}}{t}_{\alpha}\left(n-1\right) $$. Symbol $$ \overline{X} $$, *s*, and *n* are the sample mean, SD, and sample size, respectively, while *α* represents the significant level. The confidence interval of the difference between means will also be calculated by $$ \overline{X}\pm {S}_{{\overline{X}}_1-{\overline{X}}_2}{t}_{\raisebox{1ex}{$\alpha $}\!\left/ \!\raisebox{-1ex}{$2$}\right.}\left({n}_1+{n}_2-2\right) $$, in which $$ {S}_{{\overline{X}}_1-{\overline{X}}_2} $$ is the standard error of the difference of means. The adjusted Wald confidence intervals are used to estimate confidence intervals for proportions and the difference between the two population proportions [17].

IMR changes between the two groups will be compared by independent *t*-test or Mann-Whitney *U* test, while IMR changes before and after the use of salvianolate in the same group will be compared by paired *t*-test or Wilcoxon test. Analysis of covariance will be used if the baseline and follow-up IMRs are not highly correlated (*r* ≤ 0.8) [18, 19]. If the variables are not normally distributed, they will be transformed into normal distribution by logarithm. Different hypothesis testing, including *t*-test or nonparametric tests for continuous variables as well as *χ*^2^ test for categorical variables, will be used for the secondary end points assessed by the Seattle angina scale, quality of life scale, Holter electrocardiography, and 6-min walk test. The safety end point in our trial will be the abnormal blood tests including the abnormal liver function and self-reported adverse events such as dizziness and headache. The rate of abnormal liver function and other adverse events between the salvianolate group and the placebo group will be compared by *χ*^2^ test.

In our trial, stable CHD patients with myocardial microcirculatory disturbances form the population of interest, and participants with 50 to 70% stenosis in major coronary arteries, FFR > 0.80, and IMR > 25 form a sample. The end point of interest will be the IMR change in the immediate phase and the total ischemic burden assessed by the Seattle angina scale, quality of life scale, Holter electrocardiography, and 6-min walk test in the follow-up period.

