Premature discontinuation of salvianolate, loss to follow-up, and death are possible intercurrent events. As we use treatment policy strategy in our study, we will take a per-protocol analysis, as well as intention-to-treat (ITT) analysis for statistical analysis. Per-protocol analysis includes participants who complete the assigned therapy according to the trial protocol while ITT analysis includes all randomly assigned participants according to the treatment group to which they were originally assigned, regardless of the occurrence of intercurrent events. The ITT analysis will indicate how salvianolate will work in a more real-life setting. If there is evidence that the difference in the treatment depends on certain patient characteristics identified in the baseline assessment, a subgroup analysis will be performed.

The missing data before the intercurrent events will be filled with the measured values of “similar participants.” The similar patients should have the same sex and smoking history (smoker or nonsmoker). Missing values will be imputed by expectation-maximization algorithm through age, systolic blood pressure, diastolic blood pressure, fasting blood glucose, and IMR. Multiple imputation will be used in our study. *P*-value < 0.05 will be considered to indicate statistical significance. All statistical analyses will be performed using the Statistic Package for Social Science (SPSS) software package, version 18.0 (SPSS Inc., Chicago, IL, USA). The results will be published by the chief investigator and major contributors.

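### The stated 80% power belongs to a one-sided test against a margin of 8 IMR units, whereas the planned analysis tests for any difference

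*Protocol article*

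**What the plan says.** The Sample size section of the protocol article gives the inputs: "we assume *α* = 0.05, 1-*β* = 0.80, Mean_*t*_ = 20, Mean_*c*_ = 40", with a common SD of 20 and 1:1 allocation. It goes on to "suppose that a 20% IMR reduction (Δ = − 8) is considered of clinically meaningful difference". The printed formula divides by the square of the assumed mean difference minus Δ, and it uses Z at α, not at α/2. The result is "We get approximately 36 (between 35 and 36) needed patients in each group", followed by "Considering the loss rate of 10%, the total sample size will be 78 cases with 39 cases in each group".

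The End points section makes the change in IMR during the procedure the primary end point. In the Analysis section, "IMR changes between the two groups will be compared by independent" t-test or Mann-Whitney test. ANCOVA takes over if baseline and follow-up IMR correlate at 0.8 or less. The confidence interval for the difference of means uses the t quantile at α/2. A P-value below 0.05 "will be considered to indicate statistical significance". No sentence in the article sets up a test, or a rule for the interval, against −8.

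**The concern.** A power statement should describe the test that will decide the trial. Here the sample size belongs to a claim of superiority by more than 8 units at one-sided 5%, while the analysis only asks whether the arms differ.

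This is the article's only power statement for the primary end point, and Δ is the only difference it calls clinically meaningful. Two misreadings are therefore easy. A non-significant result could be taken to exclude an effect of 8 units. A significant result could be taken to show a reduction of more than 8 units. The planned test supports neither.

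A related gap is that the means of 40 and 20 look like IMR levels, since 8 is 20% of 40, while the end point is a change. The article does not say whether the SD of 20 belongs to levels or to change, and the power depends on which it is.

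**Working it through.** **Inputs** (Sample size section): means 20 and 40, SD 20, Δ = −8, α = 0.05, power 0.80, 1:1 allocation, 10% loss, 39 per group.

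**1. Reproducing the plan's figure.** The effective difference is 20 − 40 − (−8) = −12.
- One-sided, as printed: n = 2(1.645 + 0.842)² × 400 / 144 = 34.35, so 35. With the noncentral t distribution, power is 0.7996 at 35 per group and 0.8095 at 36. This matches the stated range.
- Two-sided with the margin: 2(1.960 + 0.842)² × 400 / 144 = 43.6, so 44.
- Two-sided, no margin, difference 20: 2(1.960 + 0.842)² × 400 / 400 = 15.7, so 16.
- Two-sided, no margin, difference 8: 2(1.960 + 0.842)² × 400 / 64 = 98.1, so 99.

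Of these, only the first fits.

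**2. Evaluable patients.** 39 × 0.9 = 35.1, so about 35 per arm.

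**3. Power at 35 per arm, SD 20 taken as the SD of change.** The standard error is 20 × √(2/35) = 4.78, with 68 degrees of freedom; powers are from the noncentral t distribution.

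| Test | True difference | Power |
|---|---|---|
| Two-sided 5%, null 0 | 20 | 98.5% |
| Two-sided 5%, null 0 | 13.6 (34% of 40) | 80% |
| Two-sided 5%, null 0 | 8 | 37.8% |
| One-sided 5%, null 0 | 8 | about 50% |
| One-sided 5%, null −8 | 20 | 80.0% |
| Two-sided 5%, null −8 | 20 | 69.7% |

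**4. If 20 is instead the SD of IMR levels.** The correlation r between baseline and follow-up is not given, so it is varied here as an assumption. ANCOVA has residual SD 20√(1 − r²). A t-test on change has SD 20√(2(1 − r)). Both are two-sided 5% at 35 per arm.

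| r | ANCOVA residual SD | ANCOVA power for 8 | ANCOVA difference with 80% power | Change-score t-test power for 8 |
|---|---|---|---|---|
| 0.3 | 19.1 | 41% | 13.0 | 29% |
| 0.5 | 17.3 | 48% | 11.8 | 38% |
| 0.8 | 12.0 | 78% | 8.2 | 74% |

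All three values of r fall under the plan's own ANCOVA rule, so the ANCOVA columns are the relevant ones in this case. At these values the residual SD is below 20, so ANCOVA power for the assumed 20 units is at least the 98% found in step 3.

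**The case against.** The strongest reply is that the article never claims 80% power for a true difference of 8. It sizes on an assumed difference of 20, for which the planned test has about 98% power. A reader who sees the 38% might infer that the trial is underpowered or needs more patients. The documents do not support that: for its own assumed effect the trial is larger than the planned test requires (about 16 evaluable per arm). This objection stands, and it limits the point to a mismatch of hypotheses.

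Second, no sentence says that the test is two-sided. The inference rests on the α/2 interval for the difference and the plain P < 0.05 rule, and the article's one-sample interval is written with t at α. This also stands. A one-sided test of zero would raise power for 8 units only to about 50%, and the margin would still be absent.

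Third, the 38% holds only for a t-test with 20 as the SD of change. That is correct, and it is why the ANCOVA figures are shown. Under randomisation the arms have equal expected baselines, so the difference in levels equals the difference in changes. The assumed 20 units are thus unaffected, and only the SD is in doubt.

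Fourth, one might infer that 39 per group is wrong because 36/0.9 = 40. The article says between 35 and 36, and 35/0.9 = 38.9 rounds to 39. This is a rounding choice worth about one percentage point of power.

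Finally, a reader could compare the planned confidence interval with −8, and an unseen analysis plan might state a margin test. The interval does lessen the risk of misreading. Neither possibility removes the conflict between the two sections of the article, which both appear in full.

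**Conclusion.** The point holds as an inconsistency between the hypothesis sized and the hypothesis tested. The sample-size arithmetic itself reproduces. The stated 80% is the power of a one-sided 5% test against −8, which the Analysis section does not include. For the planned comparison, the corresponding figures are about 98% at 20 units, 80% at about 13.6 units and about 38% at 8 units. They assume 35 evaluable per arm, a two-sided 5% t-test and 20 as the SD of change. If 20 is the SD of levels and ANCOVA is used, power for 8 units runs from about 41% to 78% as r goes from 0.3 to 0.8, so no single figure can be fixed until r is stated. That the stated power is not that of the planned test depends on none of these choices.

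**What to change.** Keep 78 patients and rewrite the sample-size paragraph so that it describes the analysis:

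- State whether the primary test is one-sided or two-sided.
- Say whether the SD of 20 refers to IMR levels or to IMR change.
- Restate power for the test that will be run. If ANCOVA applies, state the assumed r and give the power that follows from it.
- Choose one route for Δ. Either remove it from the formula, or, if a claim of more than 8 units is wanted, write the margin into the analysis (the whole 95% confidence interval must lie below −8). State about 70% power for that claim under the t-test with SD 20, recalculated if ANCOVA is primary.
- Minor: say that 39 per group with 10% loss leaves about 35 evaluable.

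The cost is one reworded paragraph, plus a sentence in the Analysis section if the margin is kept, submitted through the route in the Amendments section. No extra patients are needed. The downside is that the stated power for 8 units, or for the margin claim, becomes less favourable than the 80% now printed.

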### Analysis

All data will be presented as percentages, mean ± standard deviation (SD), or median (quartile range). As the population variance *σ*^2^ is unknown, the confidence interval of the population mean *μ* is calculated by the formula $$ \overline{X}\pm \frac{S}{\sqrt{n}}{t}_{\alpha}\left(n-1\right) $$. Symbol $$ \overline{X} $$, *s*, and *n* are the sample mean, SD, and sample size, respectively, while *α* represents the significant level. The confidence interval of the difference between means will also be calculated by $$ \overline{X}\pm {S}_{{\overline{X}}_1-{\overline{X}}_2}{t}_{\raisebox{1ex}{$\alpha $}\!\left/ \!\raisebox{-1ex}{$2$}\right.}\left({n}_1+{n}_2-2\right) $$, in which $$ {S}_{{\overline{X}}_1-{\overline{X}}_2} $$ is the standard error of the difference of means. The adjusted Wald confidence intervals are used to estimate confidence intervals for proportions and the difference between the two population proportions [17].

IMR changes between the two groups will be compared by independent *t*-test or Mann-Whitney *U* test, while IMR changes before and after the use of salvianolate in the same group will be compared by paired *t*-test or Wilcoxon test. Analysis of covariance will be used if the baseline and follow-up IMRs are not highly correlated (*r* ≤ 0.8) [18, 19]. If the variables are not normally distributed, they will be transformed into normal distribution by logarithm. Different hypothesis testing, including *t*-test or nonparametric tests for continuous variables as well as *χ*^2^ test for categorical variables, will be used for the secondary end points assessed by the Seattle angina scale, quality of life scale, Holter electrocardiography, and 6-min walk test. The safety end point in our trial will be the abnormal blood tests including the abnormal liver function and self-reported adverse events such as dizziness and headache. The rate of abnormal liver function and other adverse events between the salvianolate group and the placebo group will be compared by *χ*^2^ test.

In our trial, stable CHD patients with myocardial microcirculatory disturbances form the population of interest, and participants with 50 to 70% stenosis in major coronary arteries, FFR > 0.80, and IMR > 25 form a sample. The end point of interest will be the IMR change in the immediate phase and the total ischemic burden assessed by the Seattle angina scale, quality of life scale, Holter electrocardiography, and 6-min walk test in the follow-up period.

Premature discontinuation of salvianolate, loss to follow-up, and death are possible intercurrent events. As we use treatment policy strategy in our study, we will take a per-protocol analysis, as well as intention-to-treat (ITT) analysis for statistical analysis. Per-protocol analysis includes participants who complete the assigned therapy according to the trial protocol while ITT analysis includes all randomly assigned participants according to the treatment group to which they were originally assigned, regardless of the occurrence of intercurrent events. The ITT analysis will indicate how salvianolate will work in a more real-life setting. If there is evidence that the difference in the treatment depends on certain patient characteristics identified in the baseline assessment, a subgroup analysis will be performed.

The missing data before the intercurrent events will be filled with the measured values of “similar participants.” The similar patients should have the same sex and smoking history (smoker or nonsmoker). Missing values will be imputed by expectation-maximization algorithm through age, systolic blood pressure, diastolic blood pressure, fasting blood glucose, and IMR. Multiple imputation will be used in our study. *P*-value < 0.05 will be considered to indicate statistical significance. All statistical analyses will be performed using the Statistic Package for Social Science (SPSS) software package, version 18.0 (SPSS Inc., Chicago, IL, USA). The results will be published by the chief investigator and major contributors.

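### The two printed confidence-interval formulas use different t subscripts (α and α/2) under one definition of α, so their levels differ; the difference formula also prints the wrong centre

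*Protocol article*

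**What the plan says.** All of this is in the protocol article under Statistical considerations.

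- **Single mean (Analysis).** The text gives "the confidence interval of the population mean" as X̄ ± (S/√n)·t_α(n−1).
- **Symbols (Analysis).** X̄, s and n "are the sample mean, SD, and sample size, respectively", "while *α* represents the significant level". Each is defined once, and no convention for the t subscript is given.
- **Difference (Analysis).** "The confidence interval of the difference between means will also be calculated by" X̄ ± S_(X̄1−X̄2)·t_(α/2)(n1+n2−2). The multiplier is then explained as the standard error for the difference.
- **Value of α.** The Sample size section says "we assume *α* = 0.05, 1-*β* = 0.80". The Analysis section closes with "P*-value < 0.05 will be considered to indicate statistical significance". Neither place says whether the level is one- or two-sided.

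No confidence level, such as 95%, is written anywhere in the article.

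**The concern.** Two adjacent formulas use the same symbol α, but one puts α and the other α/2 in the t subscript. Both are symmetric intervals of the form estimate ± t × standard error, so the same α should enter both in the same way. As printed, an analyst who follows the formulas literally produces two intervals with different confidence levels, and a reader cannot tell which level either one carries.

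The second formula also places a single unsubscripted X̄, defined as the sample mean, at the centre of an interval meant for a difference between two means.

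What is at stake is the width and labelling of reported intervals. One example is the within-group IMR change, for which the plan also specifies a paired t-test. If the single-mean formula gives a 90% interval, that interval can exclude zero while the paired test at two-sided 0.05 does not reject. At n = 39 this happens when |t| lies between 1.686 and 2.024.

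**Working it through.** **Inputs.** α = 0.05 (Sample size; same threshold in Analysis). n = 39 per group (Sample size). SD = 20 per group and means 20 and 40 (Sample size: "Mean_*t*_ = 20, Mean_*c*_ = 40"). The SD serves only to put half-widths on the IMR scale; the percentage errors do not depend on it. The article gives no numerical interval or confidence level, so there is no stated figure to reproduce.

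**Standard errors.**
- One mean: 20/√39 = 3.203.
- Difference: 20·√(2/39) = 4.529.

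**Convention A: subscript is an upper-tail area.**
- Single mean: t_0.05(38) = 1.686, so coverage is 1 − 2 × 0.05 = 90%. Half-width 1.686 × 3.203 = 5.40.
- Two-sided 95% would need t_0.025(38) = 2.024, half-width 6.48. Ratio 1.686/2.024 = 0.833, so the interval is 17% too narrow.
- Difference: t_0.025(76) = 1.992, coverage 95%, half-width 1.992 × 4.529 = 9.02. This width is correct.

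**Convention B: subscript is a two-tail area.**
- Single mean: t = 2.024, coverage 95%. This width is correct.
- Difference: a two-tail area of 0.025 leaves 0.0125 in each tail, so t = 2.287 on 76 df, coverage 97.5%, half-width 2.287 × 4.529 = 10.36.
- Against 1.992 (half-width 9.02), the ratio is 2.287/1.992 = 1.148, so the interval is 15% too wide.

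| Convention | Single mean | Difference |
|---|---|---|
| A, upper-tail | 90% | 95% |
| B, two-tail | 95% | 97.5% |

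The levels differ in both rows. With 36 per group the result is nearly the same: 1.690/2.030 = 0.832 under A and 2.291/1.994 = 1.149 under B.

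**Which convention does the article use?** It does not say for t. The sample-size formula writes Z with subscript α, and its result of between 35 and 36 per group fits only an upper-tail area of 0.05. With |20 − 40 + 8| = 12, the normal formula gives 2(1.645 + 0.842)² × 20²/12² = 34.35, and the noncentral-t version gives 35.04. Two-sided 0.05 gives 43.60 and 44.59. This leans towards convention A, but Z and t notation can differ, so it does not settle the matter.

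**Centre of the difference interval.** At the planning values the true difference is 20 − 40 = −20. Read literally with half-width 9.02, an interval centred on the treatment, control or overall mean would run about 11.0 to 29.0, 31.0 to 49.0 or 21.0 to 39.0. None contains −20. Centred on X̄1 − X̄2, simulated coverage over 200,000 runs is 95.0%. This shows only that the printed centre cannot be what is meant.

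**The case against.** The strongest case is that these are editorial slips with almost no consequence.

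- **The centre corrects itself.** The sentence names the difference as its target, and the standard error and degrees of freedom beside it belong to a two-sample difference. Only X̄1 − X̄2 fits, and the standard two-sample procedure in the named software (SPSS) would not use a single mean. This stands. A reader might infer that the primary treatment difference will be reported with an interval of near-zero coverage, but the document does not support that, because nobody would carry out the literal version.
- **No decision rests on the formulas.** The primary comparison is by t-test, Mann-Whitney U or analysis of covariance, judged at P < 0.05. The sample size uses its own equation. This also stands. Nor does the article mention error bars: its stated descriptive summaries are percentages, mean with SD, or median with quartile range.
- **The 95% level is not in the text.** True, so calling one interval wrong measures it against an inferred level. The inconsistency itself does not need that inference, because whatever level was intended, one α entered in two ways cannot give it in both formulas.
- **Software will settle the width.** Only in part. The user sets the confidence level in the software, and the article never names one.

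A reader might also infer that the interval on the primary difference has the wrong width. That follows only under the two-tail convention, and the interval is then conservative. Under the upper-tail convention its width is right, and only the single-mean interval is affected.

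**Conclusion.** The point holds as an inconsistency in stated analysis formulas, of modest practical weight. Under one definition of α, the single-mean and difference intervals have levels of 90% and 95%, or of 95% and 97.5%, depending on the t convention. The size is either a single-mean interval 17% too narrow or a difference interval 15% too wide. These are alternatives and cannot both apply. The printed centre of the difference interval is a separate and evident notation slip.

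The conclusion rests on two assumptions: that α = 0.05 applies to the intervals, and that two-sided 95% is the intended level, which is inferred from α and the P < 0.05 threshold. The documents do not support reading this as a flaw in the hypothesis tests, the sample size or the trial's decision rule.

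**What to change.** In the Analysis section:

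1. State that all confidence intervals are two-sided 95%, with α = 0.05 and t_(α/2) denoting the value with upper-tail area α/2.
2. Write the single-mean interval as X̄ ± t_(α/2)(n−1)·S/√n.
3. Write the difference interval as (X̄1 − X̄2) ± t_(α/2)(n1+n2−2)·S_(X̄1−X̄2).

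At 39 per group and SD 20, both are then 95% intervals, with half-widths of 6.48 and 9.02. The cost is a correction to two formulas and one added sentence. No test, sample size or data collection changes.

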### End points

The primary end point will be the IMR change in the immediate phase during the coronary angiography procedure, and the secondary end points will be the total ischemic burden assessed by the Seattle angina scale, quality of life scale, Holter electrocardiography, and 6-min walk test after 7 days before discharge. The safety end point will be the abnormal blood tests and self-reported adverse events.

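### The only interval given for a difference between means is the unadjusted two-sample t interval, which fits the t-test but not the ANCOVA used for IMR when r ≤ 0.8

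*Protocol article*

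**What the plan says.** The End points section defines the primary outcome: "The primary end point will be the IMR change in the immediate phase during the coronary angiography procedure".

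The first paragraph of the Analysis section sets out interval methods in general terms, for a single mean, for a difference between means, and for proportions. For the second it says "The confidence interval of the difference between means will also be calculated by" a formula with t on n1+n2−2 degrees of freedom, whose standard error is that of the difference of means. The formula has no covariate term, and no exception is made for any outcome or model. IMR is not mentioned in that paragraph.

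The second paragraph turns to the tests for IMR: "IMR changes between the two groups will be compared by independent *t*-test or Mann-Whitney *U* test". It then adds "Analysis of covariance will be used if the baseline and follow-up IMRs are not highly correlated", with the threshold set at r ≤ 0.8. No estimate or interval is given for the ANCOVA.

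**The concern.** An ANCOVA P-value refers to the baseline-adjusted treatment difference, its residual standard error and n1+n2−3 degrees of freedom. The written interval uses the unadjusted difference, a standard error that gains nothing from the baseline value, and n1+n2−2 degrees of freedom. An analyst who followed both sentences literally would print a P-value from one model beside an estimate and interval from another.

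Two things are at stake. The reported interval would be wider than the analysis supports. It could also contain zero when the test is significant, or exclude zero when the test is not. Readers will probably set the interval against the 8-unit reduction that the Sample size section calls clinically meaningful, so its width matters for interpretation.

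**Working it through.** **Inputs from the documents (Sample size section).** Significance level 0.05 and power 0.80; SD 20 in each group; means 20 and 40, so a planned difference of 20; Δ = −8; 39 patients per group.

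**The plan's own figure.** The plan states no interval width, so the only figure to reproduce is the sample size. The denominator is (20 − 40 + 8)² = 144. With one-sided α, n = 2 × (1.645 + 0.842)² × 400 / 144 ≈ 34.4, or 35 per group (36 with a t-based calculation), which agrees with the stated range of 35 to 36. Allowing for 10% loss, 35 / 0.9 = 38.9, or 39 per group. Sidedness is a separate matter and does not affect this point.

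**Assumptions.** Baseline and follow-up IMR are bivariate normal with SD 20 at both times. The correlation r is not in the documents, so I use 0.3 to 0.8, within the region where ANCOVA applies. I centre the t interval on the difference between group mean changes, because change is the primary outcome.

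**Formulas.** With n per arm and common SD σ, ignoring the small term for chance baseline imbalance:
- change-score SE = σ × √(2(1 − r)) × √(2/n)
- ANCOVA SE = σ × √(1 − r²) × √(2/n)
- ratio = √(2(1 − r) / (1 − r²)) = √(2 / (1 + r))

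The ratio is √(2/1.3) = 1.24 at r = 0.3, √(2/1.5) = 1.15 at 0.5, √(2/1.7) = 1.08 at 0.7, and √(2/1.8) = 1.05 at 0.8.

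Example at r = 0.5 and n = 39: √(2/39) = 0.2265. The change-score SE is 20 × 1 × 0.2265 = 4.53 and the ANCOVA SE is 20 × 0.866 × 0.2265 = 3.92. Multiplying by t ≈ 1.99 gives half-widths of about 9.0 and 7.8.

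**Simulation.** 39 per arm, 40,000 trials per setting, two-sided 0.05. Disagreement means that the ANCOVA test and the unadjusted 95% interval differ about zero.

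| r | Mean half-width, unadjusted vs ANCOVA | Wider by | Disagree, true difference 8 | 12 | 20 |
|---|---|---|---|---|---|
| 0.3 | 10.6 vs 8.6 | 23% | 22% | 23% | 4% |
| 0.5 | 9.0 vs 7.8 | 15% | 19% | 15% | 1% |
| 0.7 | 7.0 vs 6.5 | 8% | 13% | 5% | 0% |
| 0.8 | 5.7 vs 5.4 | 5% | 8% | 1% | 0% |

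Most disagreements have ANCOVA significant and the interval containing zero (at r = 0.3 and difference 8, 17.5% against 4.6% the other way). With no true effect, disagreement is 3% to 5%. Coverage of the unadjusted interval was 94.8% to 95.3% throughout, so it is valid.

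**Reading against 8 units.** Moving the reference value from 0 to 8 shifts both intervals alike. At a true difference of 20 they therefore disagree about excluding 8 as often as they disagree about zero at a true difference of 12 (20 − 8 = 12), about 1% to 23%. The Analysis section plans no test against 8, so this concerns interpretation only.

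**The case against.** The strongest reply is that the article never says an ANCOVA P-value will be reported with the t interval. The formula sits in a general paragraph, is not labelled for IMR, and is the correct partner of the independent t-test, the first between-group test named for IMR change. ANCOVA output supplies its own adjusted difference and interval, so an analyst may report that by default. A condensed article may also leave such detail to a fuller plan.

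Much of this stands, and it rules out some stronger readings that a reader might infer:

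- *That the protocol commits to the t interval for the primary IMR result.* It does not. The rule is generic and reaches IMR only because no other rule for a difference in means is given.
- *That the interval would be invalid or biased.* It would not. Under randomisation the change-score difference estimates the same treatment effect with nominal coverage. It is only less precise.
- *That the interval ignores chance baseline imbalance.* For a change score the opposite is true. The baseline difference is subtracted in full, which over-corrects relative to ANCOVA when r < 1 and the SDs are equal.
- *That a conflict with the P-value is likely at the planned effect.* At a difference of 20 it is rare, 0% to 4%.

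What does not stand is the claim that this is mere silence. The article writes out a standard error and degrees of freedom for a difference in means without exception, and then names an analysis that they do not fit.

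It may also be said that the real problem is the data-dependent choice of test. That is a separate issue, and settling it in favour of ANCOVA would not by itself change the written interval rule.

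**Conclusion.** The point holds in limited form. The stated interval matches the t-test branch and not the ANCOVA branch. Applied to IMR as written when r ≤ 0.8, it would be valid but about 5% to 23% wider than the ANCOVA interval. It could disagree with the ANCOVA P-value about zero, materially so for true differences of 8 to 12 with low or moderate r, and hardly at all at the planned difference of 20.

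These sizes rest on SD 20 at both times, normal data, 39 per arm and an assumed r. Eligibility requires IMR > 25, which truncates baseline, so equal SDs and normality are approximations. The direction does not depend on equal SDs. With baseline SD σx and follow-up SD σy, the change-score variance minus the ANCOVA residual variance is (σx − rσy)², which is never negative. Apart from the small cost of one degree of freedom and the imbalance term, the unadjusted interval is therefore never the narrower one.

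**What to change.** Add one sentence to the Analysis section: when ANCOVA is used, the IMR treatment difference and its 95% confidence interval are the baseline-adjusted difference and interval from that same model, with its residual standard error and degrees of freedom. State that the two-sample t interval applies to unadjusted comparisons.

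This costs one sentence. Standard ANCOVA output already gives the estimate and interval. The sample size, data collection and trial conduct do not change.
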